Many reports have presented the inhibitory effects of statins on cardiovascular events. Yet according to the sixth annual interim report on the Japan Diabetes Complications Study (JDCS) published in 2004, the incidence rates of ischemic heart disease and cerebrovascular disease in diabetic populations were 6.7 / 1,000 humans per year and 6.5 / 1000 humans per year, or 3-4 times higher than the rates in the non-diabetic patients reported in the Hisayamacho study. Even now, the onset of cardiovascular events in patients with type 2 diabetes has become a major problem.

LDL cholesterol, a major risk factor for arteriosclerosis, comes from two sources: synthesis in the liver and absorption from the small intestine. Statins, the current first-line therapy for dyslipidemia, work mainly by inhibiting cholesterol synthesis in the liver. Statins have been reported to inhibit cardiovascular events and are confirmed to reduce various inflammatory markers in patients with type 2 diabetes. Recent progress in molecular biology has also made headway towards another clinical target, suppressing cholesterol absorption. Specifically, an inhibitor of the cholesterol transporter NPC1L1 expressed in the proximal portion of the small intestine has been found to inhibit cholesterol absorption in clinical studies. Ezetimibe, an agent that suppresses cholesterol absorption by binding to NPC1L1, has been accepted for clinical application in Japan since last year. According to clinical studies overseas, a combination of ezetimibe and statin is capable of conferring better control in the treatment of dyslipidemia compared to a stronger dose of statin.

Yet as of the present, there have yet to be appropriate reports in Japan on clinical results attained from the combination of the cholesterol absorption inhibitor ezetimibe with statins.

2. Purpose and needs of the study

1. Purpose

To evaluate the effect of combination therapy with ezetimibe and statin on type 2 diabetic subjects with hypercholesterolemia. The anti-inflammatory effects will be revealed by measuring inflammatory markers in both groups at the same time.

1. Needs of the study and clinical significance

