The discovery of a more potent treatment for type 2 diabetics with hypercholesterolemia could lead to the establishment of a useful therapy with pleiotropic effects for type 2 diabetics overall. It may also be possible to further improve the therapeutic effects on type 2 diabetics by understanding how the combination treatment of ezetimibe and statin influences inflammatory markers predictive of cardiovascular events.

1. 3. Brief overview of the study drugs
2. Atrovastatin calcium tablet

Trade name: Lipitor tablet 5 mg and 10 mg

Generic name: Atrovastatin calcium hydrate

1. Pitavastatin calcium tablet

Trade name: Livalo tablet 1 mg and 2 mg

Generic name: Pitavastatin calcium tablet

1. Ezetimibe

Trade name: Zetia tablet 10 mg

Generic name: ezetimibe tablet

1. Study patients

Patients who meet the following entry criteria without meeting any of the following exclusion criteria

1. Entry criteria
2. Type 2 diabetes mellitus
3. Has used atorvastatin 10 mg/day or pitavastatin 1 mg/day for >1 month
4. LDL-C ≥120 mg/dL for patients without CAD; LDL-C ≥100 mg/dL for patients with CAD
5. Age ≥20 years

(2) Exclusion criteria

1. History of hypersensitivity to atorvastatin, pitavastatin, or ezetimibe
2. Triglyceride ≥400 mg/dL
3. Hepatic dysfunction (ALT> 2 x upper limit of normal range in each hospital)
4. Poor glycemic control (HbA1c > 9.4 %)
5. Renal dysfunction (serum creatinine ≥2.0 mg/dL)
6. Secondary dyslipidemia, drug-induced dyslipidemia
7. Homozygotic familial hypercholesterolemia
8. Pregnant, able to conceive children, or breastfeeding
9. Another non-specific reason, such as poor adherence

5. Policy and procedure for explaining the study and obtaining consent

Sub-investigators will give each patient a consent document with descriptions of the study approved by the Institutional Review Board of the University and thoroughly explain the content of the document to the patient verbally. After discussion and an exchange of questions and further explanations, the patient will provide his or her voluntary written consent to participate in the study.

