Doses were determined according to the product documentation. The subjects will take ezetimibe postprandially, as the product documentation for ezetimibe states: “Ezetimibe prescribed for adults is usually given once a day at a 10 mg dose postprandially.”

1. Rules for combination therapy
   1. Prohibited drug combinations
2. Lipid-lowering agents (except for the study drugs):

HMG-CoA reductase inhibitors, anion-exchange resins, fibrates, nicotinate, EPA, probucol, and other lipid-lowering agents are not to be taken in combination with the study drugs.

To evaluate the efficacy and safety of the study drugs precisely.

1. Cyclosporine

The combination of cyclosporine and pitavastatin is contraindicated. The combination of cyclosporine with atorvastatin or ezetimibe leads to high serum levels of these drugs, which increases the risk of side effects.

- 1. Drugs acceptable for combination therapy

Drugs for complications and adverse events can be used as prescribed. All drugs used must be described on the examination sheets.

1. Methods of registration and assignment

The sub-investigators will check to confirm that the patient meets the inclusion criteria and does not meet the exclusion criteria. Next, the doctors will (1) obtain the patient’s voluntary written consent to enroll in this study, (2) fill in the “registration sheet” to pair the subject with an identification number, (3) fix the identification number and allocate the patient to a regimen by uploading the necessary data to the web, (4) fill in the indicated identification number and result of the allocations on the “registration sheet,” and preserve the sheet.

7. Endpoints

(1) Primary endpoint

The primary endpoint is the percentage change in the level of serum LDL-C from baseline at the end of the administration period.

(Basis for setting the primary endpoint)

The Japanese guideline for clinical evaluation of lipid lowering agents in 1988 suggests the rate of lipid change as a standard index for evaluation, and the rate of change in LDL-cholesterol is widely used as an index for efficacy domestically and worldwide.

(2) Secondary endpoints

The first secondary endpoint is the percentage of patients who reach the treatment goal for LDL-C at the end of the administration period.

The second secondary endpoint is the percentage change in the levels of serum lipids and inflammation markers from baseline to the end of the administration period.

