* The serum IRI values of the patients injecting insulin will not be analyzed initially, but they may be analyzed by a secondary analysis.

(basis of setting)

The Japanese “Guideline for the Prevention of Atherosclerotic Diseases (2007)” presents target lipid-lowering values for different categories classified by risk factors. Based on these values, the percentage of patients who reach the treatment goals for LDL-C at the end of the administration period will be adopted as an index of efficacy. As some serum lipids other than LDL-C are recognized as risk factors for atherosclerosis, the effects on these lipids will also be evaluated as appropriate indices of efficacy. Several inflammatory markers reported to be predictive of atherosclerosis will also be evaluated as appropriate indices of efficacy.

1. Evaluation of safety

Secondary endpoints

Adverse events and side effects

Laboratory examination

1. Definitions of adverse events and side effects

Adverse events mean any unfavorable or unintended signs (including abnormal laboratory data), symptoms, or diseases, regardless of causal associations with the study drugs. Side effects mean adverse effects that cannot be confirmed not to be causally associated with study drugs.

1. Severity of adverse events

The severity of adverse events other than fever is determined by the following criteria:

1. Slight : no trouble in daily living.
2. Intermediate (non-severe, non-slight): some restrictions in daily living
3. Severe: independent daily not possible

The severity of fever is determined by the following criteria:

1. Slight: body temperature of less than 38℃ but apparently higher than baseline
2. Intermediate: body temperature of more than 38℃ but less than 40℃
3. Severe: body temperature of more than 40℃
4. Definition of severe adverse events

The following will be treated as severe adverse events:

1. Death
2. Events that may lead to death
3. Hospital admission or extended period of hospitalization
4. Disability (permanent or remarkable disability/dysfunction)
5. Events that cause congenital anomalies or birth anomalies
6. Events that resemble any of the abovementioned states
7. Treatment adjustments for adverse events

The treatment adjustments for adverse events will be classified into three types:

1. Continuation 2. Dose reduction 3. Cessation
2. Outcome

The outcomes of adverse events will be described as follows on the case sheets:

1. Recovery (symptoms disappear)

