2. Remission (severity of symptoms decreases)
3. Recovery delay
4. After-effect (daily living is still disrupted after recovery, requiring continuous medication)
5. Death (caused by relevant adverse events)
6. Other (clarify the reason)
7. Causative association

Causative associations will be classified as follows:

1. No relation 2. Little relation 3. Undeniable relation 4. Related

8. Observation and examination

(1) Patient background

1) general assessment: sex, age, height, body weight, past history (stroke or cardiovascular), complications, smoking, family history of cardiovascular disease, co-administered drugs

(2) examination component

1) serum lipids: total cholesterol (TC), triglyceride (TG), LDL-cholesterol (LDL-C), HDL-cholesterol (HDL-C), RLP-C, apo A-1, apo B, apo E (baseline, 12 wk, 26 wk, 52 wk); MDA-LDL (only for patients with CHD history) (baseline, 12 wk, 26 wk, 52 wk), small dense LDL (baseline, 12 wk, 52 wk)

2) glucose metabolism: fasting plasma glucose, IRI, HbA1c (baseline, 12 wk, 26 wk, 52 wk)

3) inflammatory markers: hs-CRP (baseline, 12 wk, 52 wk)

4) biochemical: ALT, AST, γ-GTP, CPK, serum creatinine (baseline, 12 wk, 26 wk, 52 wk)

Examination schedule

|  | | observation | initial | 12 wk | 26 wk* | 52 wk* |
| --- | --- | --- | --- | --- | --- | --- |
| Acceptable range of gaps | |  |  | +4 wk | ± 4wk | ± 4wk |
| Informed consent | | **●** |  |  |  |  |
| Patient background | | **●** | |  |  |  |
| Serum lipids | TC |  | **●** | **●** | **●** | **●** |
|  | TG |  | **●** | **●** | **●** | **●** |
|  | LDL-C |  | **●** | **●** | **●** | **●** |
|  | HDL-C |  | **●** | **●** | **●** | **●** |
|  | RLP-C |  | **●** | **●** | **●** | **●** |
|  | Apo A-1 |  | **●** | **●** | **●** | **●** |
|  | Apo B |  | **●** | **●** | **●** | **●** |
|  | Apo E |  | **●** | **●** | **●** | **●** |
|  | MDA-LDL** |  | **●** | **●** | **●** | **●** |
|  | small dense LDL |  | **●** | **●** |  | **●** |
| Glucose metabolism | FPG |  | **●** | **●** | **●** | **●** |
|  | **IRI^＃^** |  | **●** | **●** | **●** | **●** |
|  | HbA1c |  | **●** | **●** | **●** | **●** |
| Inflammatory markers | hs-CRP |  | **●** | **●** |  | **●** |
| biochemistry | ALT、AST、γ-GTP、CPK、serum creatinine |  | **●** | **●** | **●** | **●** |
| Adverse events | |  | **●** | | | |

●, compulsory; *, for feasible patients only; **, for patients with CHD history only;

＃, measurement depends on the doctor’s decision in patients injecting insulin.

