The study drugs administered are covered by national health insurance in Japan. Patients will bear the self-pay portion of the health insurance examination. The cost for the investigation of the original disease will also be covered by medical insurance. However, funds must be provided to cover research expenses for measuring LDL-C, RLP-C, small dense LDL, and hs-CRP, to ensure that the patients will bear no cost burdens by participating in the study.

18. Insurance coverage and compensation for health problems resulting from the study

(1) Compensation for health damage

If any health damage is caused as a result of participation in this study during treatment at this hospital, an application will be submitted for exemption of the patient’s share of the resulting medical expenses. Such an exemption will not apply, however, to the following costs.

1. Cost of medical care that is usually administered to treat complications and underlying disease
2. Costs for treatment of health damages caused by commercially available drugs given within their indications
3. Costs for treatment when liability claims are brought on the grounds of medical malpractice, etc.
4. Insurance coverage

The investigators and sub-investigators will take out liability insurance.

19. Observance of the Declaration of Helsinki and GCP

This study complies with the "Ethical Guidelines for Clinical Research" (459 Ministry of Health, Labour and Welfare Notification No. 2004) and the "Declaration of Helsinki" (including the 2004 annotated version).

20. Storage of records

The investigators are required to store documents used for the practice of this study and to discard them five years after the publication of the study (e.g., copies of application documents, notification documents from the hospital director, copies of the various application forms and reports, registration forms, copies of consent forms, case report forms, records or documents required to ensure the reliability of the other data).

21. Publication of research results

With regard to the publication of this study, the investigators and sub-investigators will decide a publication time, a presenter, presentation methods, and the like after the clinical research is completed.

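### The protocol promises several inflammatory markers but schedules only hs-CRP, and percentage change is a poor scale for the one test that reaches it

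*Protocol*

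**What the plan says.** The protocol refers to inflammatory markers in the plural in four places.

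- Section 2, Purpose: "The anti-inflammatory effects will be revealed by measuring inflammatory markers in both groups at the same time".
- Section 2, needs and clinical significance: the hope is to understand "how the combination treatment of ezetimibe and statin influences inflammatory markers predictive of cardiovascular events".
- Section 7, secondary endpoints: "The second secondary endpoint is the percentage change in the levels of serum lipids and inflammation markers from baseline to the end of the administration".
- Section 7, basis for the secondary endpoints: "Several inflammatory markers reported to be predictive of atherosclerosis will also be evaluated as appropriate indices of efficacy".

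Two places say what will be measured.

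- Section 8(2): "inflammatory markers: hs-CRP (baseline, 12 wk, 52 wk"). The schedule table agrees and marks the 26- and 52-week visits as "for feasible patients only". Every patient is therefore scheduled for two hs-CRP values, at baseline and week 12.
- Section 17: the research funds are for "measuring LDL-C, RLP-C, small dense LDL, and hs-CRP".

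Section 14(3) assigns the Wilcoxon rank sum test to percentage change in LDL-C. For the other examination data it names the Wilcoxon signed rank test on change within each group, without saying whether change is absolute or a percentage.

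**The concern.** There are two linked problems.

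The first is scope. The anti-inflammatory evaluation is the second sentence of the stated purpose, and it is framed around several markers that predict atherosclerosis. If only hs-CRP is collected, a report written to that purpose would claim more than the data can show. A statistical analysis plan could not repair this, because it cannot add an assay that the schedule does not collect.

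The second is scale. The endpoint is percentage change, and hs-CRP is a right-skewed marker. Percentage change cannot fall below -100% but has no upper limit. The signed rank test asks whether the changes are symmetric about zero. On an asymmetric scale it can reject when nothing has changed, and it can miss a genuine fall. For a secondary objective that hopes to see hs-CRP fall, both errors matter.

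**Working it through.** **1. The plan's own figure.** Section 15 assumes LDL-C effects of 11.7% and 21.7% (difference 10 points), SD 15%, α 0.05 and power 90%. Taking α as two-sided:

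n per arm = 2 × (1.960 + 1.282)² × 15² / 10² = 47.3, rounded up to 48.

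With 20% dropout, 48 / 0.8 = 60 per arm, or 120 in total. This matches section 15. It gives 48 evaluable patients per arm, which is used below. The protocol gives no figure for hs-CRP.

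**2. Markers promised against markers scheduled.**

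| Place | Inflammatory markers |
|---|---|
| Section 2, Purpose and clinical significance | plural, unnamed |
| Section 7, second secondary endpoint | plural, unnamed |
| Section 7, basis | several, unnamed |
| Section 8(2) and schedule | hs-CRP only |
| Section 17, funded assays | hs-CRP only |

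MDA-LDL and small dense LDL do not fill the gap. Section 8 classes both as serum lipids, and MDA-LDL is measured only in patients with a history of CHD. The count is one.

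**3. Why the scale matters for a signed rank test.** Let r be the week 12 value divided by the baseline value. Percentage change is 100 × (r - 1); the log ratio is ln r.

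- Halving (r = 0.5): -50%, or -0.69 on the log scale.
- Doubling (r = 2): +100%, or +0.69 on the log scale.

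These two are equal and opposite on the log scale. On the percentage scale the doubling has the larger absolute value and so the higher rank. When rises and falls are equally likely and proportionally equal, the positive rank sum is therefore systematically too large. The test leans towards an apparent rise and works against detecting a fall.

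**4. Size of the effect, by simulation.** Assumptions: 48 patients in one group, log ratio normally distributed, no true change, two-sided 5% level. The log-SD values are assumed because the protocol gives none.

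| Assumed log-SD of change | Signed rank on percentage change | Signed rank on log ratio |
|---|---|---|
| 0.6 | about 13% reject | about 5% |
| 0.8 | about 18% reject | about 5% |
| 1.0 | about 23–24% reject | about 5% |

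For a true 25% fall at log-SD 0.8, power is about 24–25% on percentage change and about 66% on the log ratio.

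**5. Where the scale does not matter.**

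- *Absolute change.* If the two visits have the same distribution and are exchangeable, week 12 minus baseline is symmetric about zero, and the signed rank test keeps its level.
- *Rank sum test between arms.* Percentage change is an increasing function of ln r, so the ranks across the two arms are the same on either scale, and so is the p-value.

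**6. Acute illness at sampling.** None of the nine exclusion criteria in section 4 specifically covers infection or inflammatory disease, and section 8 gives one sample per time point with no repeat rule. The effect was simulated for a rank sum test between arms with 48 per arm, log-SD 0.8, and an assumed 0%, 5% or 10% of samples at each time point raised at random.

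| Samples raised | Type I error | Power, 40% reduction | Power, 25% reduction |
|---|---|---|---|
| 0% | 0.046 | 0.86 | 0.39 |
| 5% | 0.049 | 0.72 | 0.31 |
| 10% | 0.047 | 0.59 | 0.23 |

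Illness that is equally likely in both arms costs power but does not bias the comparison.

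**The case against.** The strongest reply is that this is a wording mismatch on a secondary endpoint. hs-CRP is compulsory in both arms at baseline and week 12, and patients are allocated by minimization, so the regimen effect on hs-CRP can be estimated. The significance paragraph is worded as a possibility. The efficacy tests are rank-based, which caps the influence of an extreme value. Log transformation and sensitivity analyses are commonly left to a statistical analysis plan, which is not at hand here.

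Much of this stands, and it rules out three stronger readings.

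- A reader might infer that the anti-inflammatory objective cannot be met at all. The documents do not support that: an effect on hs-CRP can be estimated. What cannot be supported is a claim about several markers or inflammation in general.
- A reader might infer that unscreened infection could mimic a regimen effect. Step 6 shows that randomly occurring illness lowers power and leaves type I error near 5% in a between-arm rank sum test. A cut-off for acute-illness values is optional detail for an analysis plan and rests on assumed figures.
- A reader might take "Drugs for complications and adverse events can be used as prescribed" to mean that other drugs may be changed at will. Section 6 prohibits other lipid-lowering agents and addresses cyclosporine under its prohibited combinations, and it requires all drugs used to be recorded.

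Two things survive. An analysis plan cannot supply markers that are not collected. And the protection offered by ranks holds for the rank sum test, which section 14 names for LDL-C only. In the signed rank test, capping the extremes does not restore symmetry, as step 4 shows. An unseen plan may add a between-arm test for hs-CRP; the protocol itself does not.

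**Conclusion.** The point holds in two parts of different certainty.

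The contradiction over markers is definite and rests on no assumption: several are promised and one is scheduled and funded. The passages need to be reconciled.

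The scale problem is conditional. It arises only if the within-group signed rank test is applied to percentage change, which is how the endpoint is defined but not how section 14 words the test. In that case the error rate with no true change is about 13% to 24% instead of 5%, and power for a 25% fall at log-SD 0.8 is about 25% instead of 66%. These figures assume 48 patients per group, a log-SD of 0.6 to 1.0 and a symmetric log ratio.

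The primary endpoint, its test and the sample size of 60 per group are unaffected.

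**What to change.** - In sections 2 and 7, restate the objective and the second secondary endpoint as the effect on hs-CRP, and drop the reference to several markers and to a general anti-inflammatory effect. If further markers were intended, they would have to be named in sections 7 and 8 and funded under section 17.
- In sections 7 and 14, analyse hs-CRP as the log ratio of week 12 to baseline instead of percentage change, and report it as a geometric mean ratio.
- Optionally, leave to the analysis plan a sensitivity analysis for values taken during acute illness. Adverse events and all drugs used are already recorded.

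Limiting the claim to hs-CRP requires changes of wording only: no new assay, visit or patient. The price is a narrower claim.

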| Analysis sets fitting the protocol  Efficacy by PPS (Per Protocol Set) | Cases with the minimum compulsory program and available values for major variables, and without crucial contraventions of the protocol | Background, efficacy, safety |
| Analysis sets for safety | Prescribed cases with at a least single evaluation for safety | Background, safety |

(3) Statistical analysis

1) analysis for efficacy

The Wilcoxon rank sum test will be performed to analyze the percentage change in the level of serum LDL-C from baseline to week 12 of treatment.

The percentage of patients who reach the treatment goals at the end of the administration period will be calculated.

Wilcoxon signed rank test will be performed to analyze the change of examination data within each group.

2) The number and frequency of adverse effects will be calculated for subjects who receive at least a single administration of the study drugs. The same counting approach will be used for side effects.

15. Target number of cases and basis for setting it

(1) Target number of cases

Number of participating institutions: 25 institutions

Target number of cases: 120 cases

(2) Basis for setting the target number of cases

The first statin dose is assumed to account for 11.7% of the LDL-C-lowering effect in the double-dose statin administration group and 21.7% of the LDL-C-lowering effect in the ezetimibe add-on group. The SD is assumed to be 15 %, with an α of 0.05 and power of 90 %. Hence, there will be 60 cases per treatment group, assuming a dropout rate of 20 %.

16. Safety, human rights, and disadvantages faced by the study subjects

(1) Steps taken to protect human rights (Protection of privacy)

The confidentiality of the subjects must be duly considered when handling raw data for the study implementation, the consent form, etc. When case reports are to be submitted out-of-hospital, they will be handled using subject identification codes or the like. When the results of tests are published, the information will be screened to ensure that it cannot be used to identify the subjects. It will also be assumed, from the outset, that data on the subjects will not be used for any purposes other than the study.

17. Cost burdens on the patients

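### Symptom-free laboratory adverse events of any size must be graded Slight, because every event except fever is graded by its effect on daily living

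*Protocol*

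**What the plan says.** Under Evaluation of safety in Protocol section 7, adverse events and laboratory examination are both listed as safety endpoints. The definition that follows brings laboratory findings into the first of these: "Adverse events mean any unfavorable or unintended signs (including abnormal laboratory data), symptoms, or diseases".

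The severity rule then opens with "The severity of adverse events other than fever is determined by the following criteria" and gives three grades:

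- "Slight : no trouble in daily living"
- "Intermediate (non-severe, non-slight): some restrictions in daily living"
- "Severe: independent daily not possible"

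Fever alone has a separate scale based on the measured value; its middle band reads "Intermediate: body temperature of more than 38℃ but less than 40℃".

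Section 8(2) lists the laboratory safety panel: "4) biochemical: ALT, AST, γ-GTP, CPK, serum creatinine (baseline, 12 wk, 26 wk, 52 wk". The values at baseline and week 12 are compulsory; weeks 26 and 52 are for feasible patients only.

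Section 14(3) names a rank sum test for LDL-C and, under the efficacy item, a further test: "Wilcoxon signed rank test will be performed to analyze the change of examination data within each group". Item 2) of the same section summarises adverse events and side effects by number and frequency.

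**The concern.** The grade records how far an event disrupts the patient's day. That suits symptoms. It does not suit an enzyme or creatinine value, which can be far out of range in a patient who feels well. Since the rule has only one exception, a marginal ALT rise and a many-fold ALT rise get the same grade if neither causes symptoms.

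At stake is the safety description of doubled statin against statin plus ezetimibe. Laboratory examination is a named safety endpoint and the panel consists of liver enzymes, CPK and creatinine. If events are later described by severity, the laboratory part will sit almost entirely in the lowest grade by construction, whichever regimen is involved.

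**Working it through.** **Step 1: grading (no arithmetic).** Section 7 makes three statements that combine as follows.

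1. An abnormal laboratory value is an adverse event.
2. Every adverse event other than fever is graded on the daily-living scale. No other exception and no investigator discretion is stated.
3. Intermediate needs some restriction of daily living. Severe needs loss of independent daily living.

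A laboratory rise without symptoms or restriction fails both higher criteria, so Slight is the only grade left. The size of the rise does not enter.

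**Step 2: group size for the next check.** Section 15 assumes LDL-C effects of 11.7% and 21.7% (difference 10 points), SD 15%, α 0.05, power 90% and 20% dropout. Taking α as two-sided:

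n = 2 × (1.960 + 1.282)² × 15² / 10² = 47.3, rounded up to 48; 48 / 0.80 = 60 per group.

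This reproduces the plan's 60. I use 60 (all enrolled) and 48 (completers) below.

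**Step 3: does the signed rank test respond to a few extreme rises?** Suppose changes are otherwise symmetric about zero and the two largest absolute changes are both rises.

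- SD of the statistic = √[n(n+1)(2n+1)/24]. For n = 60: √(60 × 61 × 121 / 24) = 135.8. For n = 48: √(48 × 49 × 97 / 24) = 97.5.
- Excess of the statistic over its null mean = half the sum of the top two ranks. For n = 60: (59 + 60)/2 = 59.5. For n = 48: (47 + 48)/2 = 47.5.
- z = 59.5/135.8 = 0.44, two-sided p about 0.66; z = 47.5/97.5 = 0.49, p about 0.63.

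Two patients are 2/60 = 3.3% of an arm.

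**Step 4: simulation.** There were 3,000 simulated arms per setting. Typical changes were normal with mean 0 and SD 8 U/L, and k patients had an added rise of 100 or 1,000 U/L. The SD and the rises are my assumptions; the protocol gives none. The table shows the chance of p < 0.05, as the range over the two sizes of rise.

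| Patients with a large rise (k) | 60 per arm | 48 per arm |
|---|---|---|
| 0 | 5% | 4–5% |
| 1 | 5% | 5% |
| 2 | 6–7% | 6% |
| 3 | 7–8% | 9% |
| 5 | 16% | 18–19% |
| 8 | 34–36% | 44% |
| 10 | 54–55% | 66% |

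The size of an extreme rise drops out, because only its rank counts. Replacing one patient's change with +100, +300 or +1,000 gave the same statistic (829) and the same p (0.527) each time.

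**Step 5: event counts.** Number and frequency under 14(3)2) give each event equal weight, so a small and a large rise each add one.

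**The case against.** The strongest reply is that nothing is lost. The event is counted, and its causality, treatment adjustment and outcome are recorded. Section 10 requires a precise description in the case report form. The laboratory values themselves are kept. Section 10(2) also lets a medically critical event count as a severe adverse event without admission, and prompt reporting follows that list, not the grade. All of this stands. None of it changes the grade: the severe-event lists are a separate classification by outcome or medical importance, not by laboratory value, and a large silent rise need not meet them.

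Second, the signed rank sentence sits under efficacy. The protocol nowhere says that the test is meant to detect individual toxicity, and a test of group location is not designed for that. This also stands. Steps 3 and 4 therefore show only that the test does not compensate for the grading rule, not that it is an error in itself.

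Third, counts by size of change and shift tables are commonly left to a statistical analysis plan, which is not shown here. Their absence is no finding. Such a table would, however, leave the protocol's grade as it is.

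A reader might go further and infer that the trial will report both regimens free of severe laboratory harm, or that the named test can never show such cases. The documents do not support either. No table by severity is planned in the protocol, the events remain in the counts and the data, and with about 10 of 60 patients affected the test would show a group shift in roughly half of trials.

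**Conclusion.** The point holds as a defect in a rule that the protocol itself fixes. A symptom-free rise in any of the five safety analytes, whatever its size, must be graded Slight, so the recorded grade and any summary that uses it understate laboratory toxicity. This conclusion rests on the wording of section 7 alone and needs no assumption about how often such rises occur.

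The supporting point is narrower. Of the analyses named in 14(3), the counts ignore magnitude. The within-group test does not compare arms, and with one to three extreme patients per arm it rejects in about 5–9% of simulated cases, against about 5% with none. Those percentages assume otherwise symmetric changes and my illustrative SD of 8 U/L; the z values of 0.44 and 0.49 need only the symmetry.

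The primary efficacy comparison is not affected. The change is worth making because it is cheap and concerns a named safety endpoint.

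**What to change.** In section 7, exempt laboratory adverse events from the daily-living scale, as fever already is, and add a scale based on the measured value. Multiples of each hospital's upper limit are one natural unit, since the ALT exclusion criterion in section 4 already uses them; creatinine could stay in absolute units, as in its own exclusion criterion. The cut points are a clinical decision for the investigators and should be fixed before the data are examined. Because patients may enter with ALT up to twice the upper limit, the rule should also say how a value already abnormal at baseline is graded.

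In 14(3)2), report by arm the number of patients in each laboratory grade for each test. The signed rank test can stay as a description of group change.

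Cost: amended wording in the protocol and case sheet, and one added table. No new samples are needed. The one practical burden is that reference limits must be recorded per hospital for each test graded that way; the protocol refers to a hospital limit only for ALT at entry.
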